#### Sample size

Sample size calculation was carried out with the software PASS 2015, using two independent proportions and is based on the assumed increase in the proportion of non-conspicuous parent among the initially conspicuous parents according to SCID-I criteria between the patients treated with CARE-FAM and patients that did not receive CARE-FAM at18 months after randomization. Additionally, we assume the same effect size between patients with and without WEP-CARE. Furthermore, we suppose that the two interventions work independently of each other. Given a power of 80% and a type I error rate of 5% (two-sided hypothesis), 74 initially conspicuous parents per treatment combination group (296 in total) are needed to detect a difference of 11.2% (91.2% of the CARE-FAM patients and 80% of the non-CARE-FAM patients) in the proportion of non-conspicuous parents between both groups. We further assume that at the beginning of the study 30% of the parents are conspicuous. So, at the end of the study, a total of 988 parents must be available for evaluation. Additionally, we expect a dropout rate of 20% between baseline and follow up. To compensate for this, a total of 1236 parents must be recruited. This means that a total of 618 (rounded up to 620) families (310 per stratum CARE-FAM yes/no, 155 families per group of the four randomization groups: CARE-FAM only, WEP-CARE only, combination, no study intervention) has to be included in the trial.

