#### Randomization and blinding

Computerized lists for familywise randomization with variable block length stratified by recruitment centers are prepared by the Department of Medical Biometry and Epidemiology of the University Medical Center Hamburg-Eppendorf. According to a 2x2 factorial study design, each family is randomized to one of four combinations of the two interventions (CARE-FAM only, WEP-CARE only, combination, no study intervention). The subsequent central allocation procedure will be managed by the coordinating study center in Hamburg to guarantee allocation concealment. Randomization will take place once the standardized baseline diagnostics are complete. Thus, every randomized family received comprehensive standardized diagnostics of every participating child and parent. This will maintain the families’ interest in the study and enhance retention. Although families will be aware of the group they have been assigned to, the external raters assessing the primary outcome and the health-economics will be blinded regarding the families’ group allocation to avoid detection bias by project members.

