The primary outcome, parent’s psychopathology measured by the SCID-I, is evaluated according to the intention-treat (ITT) principle. The ITT population consists of all randomized families for which baseline documentation is available. As the members of a family live under common conditions and interact with each other, cluster effects can be assumed. Thus, the inferential statistics are performed with mixed models. The primary outcome is binary (diagnosis according to SCID-I yes/no). A mixed logistic regression with family and family member as random effects, recruitment center, therapy group (2 factors: 1st factor CARE-FAM yes/no, 2nd factor WEP-CARE yes/no), and time as fixed effects within the ITT population of all initially conspicuous parents is performed. The interactions between time and the therapy groups is determined. If they are not significant, they are eliminated from the model. Missing values are treated by direct imputation to allow an ITT analysis. Under the assumption of two stochastically independent interventions, the contrast of each group factor at T4 is tested at the 5% level (two-sided hypothesis). Thereby, each intervention can prove to be effective on its own. Only these results are interpreted in a confirmatory manner. In an additional analysis, we test the assumption of independence by examining the interaction between both therapy group factors. The primary analysis is repeated in the per protocol population, which consists of all families with at least three sessions in CARE-FAM or WEP-CARE. To assess the effect of the interventions within specific subgroups, the following subgroup analyses are performed regarding study center, disease of children, age of the children, and disease of parents. In a series of sensitivity analyses, missing values are imputed by different approaches as last observation carried forward, multiple imputation, worst- and best-case imputations. Secondary outcomes are investigated exploratively without adjustment for multiplicity in the ITT population. The analysis strategy for the secondary, binary outcomes is the same as in the primary analysis. For secondary, continuous outcomes, linear mixed models with differences to baseline as outcome, family and family member as random effects and the same fixed effects as in the above-mentioned model and respective baseline value as covariate are examined. The safety outcomes are determined using frequency tables and if possible, with mixed logistic regression analogue to the primary analysis. Odds ratios or adjusted means, their 95% confidence interval, and *p* values are reported according to the CONSORT statement. Interim analyses are not planned. Statistical analyses will be carried out with standard statistical software.

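### The sample size treats parents as independent although the protocol assumes family clustering, so the stated 80% power is somewhat too high

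*Protocol article*

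**What the plan says.** Under Sample size, the article states: "Sample size calculation was carried out with the software PASS 2015, using two independent proportions". It plans for 91.2% against 80% of initially conspicuous parents being non-conspicuous at 18 months, with 80% power and a two-sided 5% level, and concludes that "74 initially conspicuous parents per treatment combination group (296 in total) are needed". It then assumes that "at the beginning of the study 30% of the parents are conspicuous", allows for 20% dropout, and arrives at 1236 parents. These become 618 families, rounded up to 620 ("310 per stratum CARE-FAM yes/no, 155 families per group of the four randomization groups"), which implies two parents per family.

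Under Randomization and blinding, the unit allocated is the family: "Computerized lists for familywise randomization with variable block length stratified by recruitment centers".

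Under Data analysis, the article gives its reason for using mixed models: "As the members of a family live under common conditions and interact with each other, cluster effects can be assumed". The primary model has a family random effect and is restricted to initially conspicuous parents.

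The article gives no intra-family correlation, no design effect and no reason for leaving one out.

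**The concern.** The sizing step assumes what the analysis section rejects. Two conspicuous parents in one family share the allocation and probably part of the outcome, so together they carry less information than two unrelated parents. If the calculation has no slack, any positive correlation takes it below its target. The 80% figure belongs to the trial's only confirmatory tests, the two factor contrasts at 18 months, and a null result on either would be read against it.

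**Working it through.** **Inputs from the article.** Proportions 0.912 and 0.80; two-sided 5% level; 74 conspicuous parents per cell, hence 2 × 74 = 148 per level of each factor; 30% conspicuous at baseline; 20% dropout; two parents per family.

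**Inputs not in the article (assumptions).** The ICC of the 18-month outcome between two conspicuous parents of one family, and the correlation φ between partners' baseline statuses.

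**1. Reproduce the plan's figure.** Exact enumeration of the two-sided z-test (unpooled variance) for 0.912 against 0.80 gives power 0.7999 at 148 per level. Normal approximations at 148 give 78.7% (pooled) and 79.4% (unpooled). So 74 per cell is the answer for independent parents.

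**2. Look for a hidden allowance.**
- 74 / 0.30 = 246.7, rounded up to 247; 247 × 4 = 988.
- 247 / 0.80 = 308.75, rounded up to 309; 309 × 4 = 1236.
- 1236 / 2 = 618.

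Every printed figure is accounted for, with no factor left over for clustering.

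**3. Look for reserve.** 620 × 2 × 0.80 × 0.30 = 297.6, about 298 conspicuous parents against 296 needed.

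**4. Effective cluster size.** Only conspicuous parents are analysed, so most clusters have one member.
- Share of families with two conspicuous parents: 0.30² + φ × 0.30 × 0.70.
- Weighted cluster size: m* = (share with one + 4 × share with two) / 0.60.
- φ = 0: 9% with two, 42% with one; m* = (0.42 + 0.36) / 0.60 = 1.30.
- φ = 0.3: 15.3% with two, 29.4% with one; m* = (0.294 + 0.612) / 0.60 = 1.51.

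**5. Design effect and power.** DE = 1 + (m* − 1) × ICC. Effective n per level = 148 / DE. Power is by exact enumeration at the nearest whole n. Parents for 80% = 296 × DE, rounded up.

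| φ | ICC | DE | Effective n per level | Power | Conspicuous parents for 80% |
|---|---|---|---|---|---|
| 0 | 0.1 | 1.03 | 144 | 78.8% | 305 |
| 0 | 0.2 | 1.06 | 140 | 77.5% | 314 |
| 0 | 0.3 | 1.09 | 136 | 76.1% | 323 |
| 0.3 | 0.1 | 1.05 | 141 | 77.8% | 312 |
| 0.3 | 0.3 | 1.15 | 128 | 74.2% | 342 |
| 0.3 | 0.5 | 1.26 | 118 | 70.9% | 372 |

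The last row is an extreme case, because it needs a high ICC and a partner-status correlation of about 0.3 together.

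**6. Detectable difference.** Holding the comparator at 80% and power at 80%, the detectable difference is about 11.5 points at effective n 140 (φ = 0, ICC 0.2) and about 11.7 points at 136 (φ = 0, ICC 0.3), against 11.2 in the plan.

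**The case against.** The strongest reply is that the loss is small and its size unknown. With no ICC and no rate of doubly affected couples in the article, a reader might infer that the trial flatly fails to deliver 80% power; the documents do not support a statement that firm. The same holds for a full two-parent design effect of 1 + ICC, which would put power near 68% at ICC 0.3. That supposes every analysed parent has an analysed partner, whereas with independent statuses only 30% do.

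Other features also reduce clustering. If dropout strikes individuals rather than whole families, the share of analysed parents with an analysed partner falls from 0.30 to 0.30 × 0.80 = 0.24, and power at ICC 0.1 to 0.3 is about 79% to 77%. Single parents are eligible and families choose who takes part, so there will be fewer pairs; that also lowers the number of parents, which is a separate matter. The model uses the 6- and 12-month data and drops non-significant time interactions, which may recover some precision. One therefore cannot assert that its standard error must exceed the planning value, although the article does not claim this as an offset.

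Nor does the omission make the analysis invalid: the family random effect is in the primary model, and no figure in the chain is miscalculated.

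These points limit the size and severity. They do not remove the inconsistency or create reserve in the calculation. Condensation of a longer protocol does not explain it either. A reason for omitting clustering could stand in the full document, but the printed chain leaves no room for a design effect.

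**Conclusion.** The point holds in moderate form. The calculation reaches 80% only at zero within-family correlation and has practically no reserve, while the protocol itself expects correlation. The direction follows from the article; the size is conditional on assumption. The loss is about 1 to 4 points for ICC 0.1 to 0.3 with independent partner statuses, and about 2 to 6 points if those statuses correlate at about 0.3. About 71% is a corner case and should not be quoted as the expected result. These figures use a simple design-effect approximation to the 18-month comparison of proportions, not a simulation of the planned mixed model. This is a should-fix point about a stated planning figure; it affects neither type I error nor the choice of analysis.

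**What to change.** In the Sample size section, state an assumed intra-family correlation for the 18-month SCID-I outcome and the expected number of conspicuous parents per family. With independent statuses the latter is 0.60 per family, or 0.60 / 0.51 = 1.18 per family that has at least one. Apply the resulting design effect and report one of the following:

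- the power of the planned 296 conspicuous parents, about 79% to 76% for ICC 0.1 to 0.3 with independent statuses; or
- the difference detectable with 80% power, about 11.5 to 11.7 points at ICC 0.2 to 0.3.

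If the sponsor prefers to keep 80%, the text should say why clustering can be neglected, for instance by quantifying any gain expected from the repeated assessments.

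The cost is a few sentences and a slightly less favourable stated figure. Enrolment, conduct and the primary model stay as they are.

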### Participants

Participants will be recruited from in- and outpatient departments of pediatric hospitals in the 17 participating study centers. Pediatricians will be asked to inform their rare disease patients and the patients’ families about the project and encourage them to contact the study team. Once families have expressed their interest to participate in the study, a member of the research staff will approach the respective families and inform them about the project.

Once all participating family members have provided written informed consent, the baseline questionnaires and interviews will be conducted. An overview of the inclusion and exclusion criteria is given in Table 1. Families with at least one child with a rare disease aged from 0 to 21 years will be included. Families can decide for themselves which family members want to participate; however, all family members will be encouraged to take part in the study. Both couples as well as single parents can take part in the study. Participation is not limited to biological parents; adoptive parents, stepparents as well as foster parents may enter in the study. To compensate for their time conducting the interviews and filling in the questionnaires, each family will receive a financial compensation of €50 if all follow-up assessments are completed.

**Table 1 Tab1:** Inclusion and exclusion criteria

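### The step from 1236 parents to 620 families assumes two participating parents in every family, although single parents and partial participation are allowed, so the stated sample and power are probably optimistic

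*Protocol article*

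**What the plan says.** The Sample size section of the protocol article works in parents until its last step. The basis is given as follows: "Sample size calculation was carried out with the software PASS 2015, using two independent proportions". It needs 74 initially conspicuous parents in each of the four groups, 296 in all, to detect 91.2% versus 80% non-conspicuous at 18 months with 80% power and a two-sided 5% level. The next assumption is prevalence: "We further assume that at the beginning of the study 30% of the parents are conspicuous". Hence "at the end of the study, a total of 988 parents must be available for evaluation". A 20% dropout after baseline raises this to the recruitment figure, and the conversion to families follows at once: "a total of 1236 parents must be recruited. This means that a total of 618 (rounded up to 620) families". The operative target is then stated in families: 310 per level of CARE-FAM and 155 per randomised group.

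The Participants section describes who may enrol. "Both couples as well as single parents can take part in the study", and "Families can decide for themselves which family members want to participate", although the same sentence adds that everyone in the family will be encouraged to join. Adoptive, step- and foster parents are also eligible.

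**The concern.** The last conversion uses a divisor of exactly two and does not say so. A mean of two is hard to reconcile with eligibility rules that expressly admit families with one parent and families in which one of two parents declines. The error runs in one direction, because Table 2 lists only mother and father as parent sources, so families with more than two participating parents cannot be relied on to offset the others.

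The primary analysis is confirmatory for both factors and is confined to initially conspicuous parents. The number of such parents drives the power of both tests. A trial could enrol all 620 families, report its target as met, and still hold fewer conspicuous parents than its own calculation requires.

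**Working it through.** **Inputs from the Sample size section:** 0.912 versus 0.80; two-sided alpha 0.05; power 80%; 74 conspicuous parents per group, which is 148 per factor level; 30% conspicuous at baseline; 20% dropout; 1236 parents; 618 rounded to 620 families. **Assumed, because the documents do not give it:** s, the share of families enrolling one parent, with all others enrolling two. The mean number of parents per family is then 2 − s.

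**1. The plan's own figures.** Exact binomial enumeration of the two-sample z-test at 148 per factor level gives power 0.7998, so the stated 80% reproduces. The remaining steps are:
- 74/0.30 = 246.7, rounded up to 247; 4 × 247 = 988.
- 988/0.80 = 1235, stated as 1236 (4 × 309).
- 1236/2 = 618, raised to 620 = 4 × 155.

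The arithmetic is sound, and the only divisor that gives 618 is 2.

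**2. The reserve.** 620 × 2 = 1240, and 1240 − 1236 = 4 parents; 4/620 = 0.6%. The fifth one-parent family leaves 1235 parents, below 1236. The sixth leaves 1234, and 1234 × 0.8 = 987.2, below 988. The seventh leaves 1233, and 1233 × 0.8 × 0.3 = 295.9, below 296.

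**3. Yield and power with 620 families.** Parents = 620 × (2 − s). Evaluable conspicuous parents = parents × 0.8 × 0.3, half of them at each factor level. Power is exact, for the pooled and the unpooled z-test, with n per level rounded to a whole number and no clustering.

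| One-parent families (assumed) | Parents | Evaluable conspicuous | n per level | Power, pooled | Power, unpooled |
|---|---|---|---|---|---|
| Plan's requirement | 1236 | 296 | 148 | 0.800 | 0.800 |
| 10% | 1178 | 283 | 141 | 0.778 | 0.778 |
| 20% | 1116 | 268 | 134 | 0.754 | 0.762 |
| 30% | 1054 | 253 | 126 | 0.724 | 0.740 |
| 40% | 992 | 238 | 119 | 0.705 | 0.713 |

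The pooled normal approximation gives 0.768/0.745/0.721/0.694. It starts from 0.789 for 620 two-parent families, so the drop is of the same size.

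**4. Whether another allowance absorbs the shortfall.** The 20% dropout is defined as loss after baseline, so a parent who never enrols is not counted in it. The earlier steps hold only the rounding shown in step 1. Encouraging all members to join cannot give a single-parent family a second parent. Nothing in the article says that enrolment continues past 620 families until 1236 parents are reached.

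**The case against.** A reader might infer that 620 families cannot deliver the sample, or that the mean must lie below two. The documents do not support that certainty. They give no parents-per-family figure, they encourage all members to take part, they admit step-, adoptive and foster parents, and no rule caps a family at two. A mean below two is likely, but the shortfall is conditional on it.

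Each division is correct, so this is an undeclared and optimistic planning assumption and not a slip of arithmetic. The full protocol, which is not shown, may declare it. That would not remove the conflict between the figure and the eligibility rules as both stand in the article.

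The loss is modest at low shares. The unverified 30% prevalence has similar leverage: at 20% one-parent families, 296/(1116 × 0.8) = 33.2% conspicuous would restore the full number. This is true, but the plan claims no such margin.

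The primary analysis is a repeated-measures mixed model on all initially conspicuous parents, with imputation, and not a test on completers. At 40% one-parent families, 992 × 0.3 = 298 conspicuous parents would still enter it. That count includes parents who later drop out. On the same footing two-parent families would give 1240 × 0.3 = 372, and imputation does not restore all the lost information. The percentages are therefore a like-for-like reading of the plan's own calculation, not a forecast of the mixed model's power.

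It is also tempting to add a loss for correlation within families. The article gives no intra-family correlation, and that question is separate from this one.

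**Conclusion.** The point holds as a conditional one. The Sample size section fixes two parents per family, the Participants section permits fewer, and a reserve of 4 parents is negligible where single parents are expressly eligible. Once more than a handful of the 620 families enrol one parent, full recruitment is expected to fall short of the plan's own 1236, 988 and 296. For an assumed 10% to 40% of one-parent families, power falls from 80% to between about 78% and 70–71%. This rests on the plan's 30% prevalence, 20% dropout, effect size and two-proportion test, and on no family enrolling more than two parents. The type I error rate, the randomisation and the validity of the test are unaffected.

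**What to change.** In the Sample size section, state the assumed number of participating parents per family. Then restate, for 620 families, the expected evaluable initially conspicuous parents and the power at the mean number observed among families already enrolled. Use baseline data only, pooled over the four groups, so that no outcome or allocation information is involved. Baseline diagnostics precede randomisation and recruitment was still open when the article appeared, so the coordinating centre can obtain the count.

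The cost is a short change of wording and a stated power that becomes somewhat less favourable.

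Resetting recruitment to 296/0.8 = 370 conspicuous parents at baseline is a different step and is not proposed. At 30% prevalence it needs about 1233 parents, which is about 649 families at 10% one-parent families and 771 at 40%. That means enrolling more than 620, and the article requires a formal amendment for sample-size changes that may affect the conduct of the study.

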### Research procedure

In order to be able to realistically recruit the sample, recruitment will be extended to several clinics and outpatient clinics. Patients will be recruited at the above-mentioned cooperating clinics and outpatient clinics, where approved therapists can treat study patients. The project staff members will review the weekly admissions and discharge lists and/or participate in the outpatient clinic/ward conferences of the cooperating institutions. The project staff will inform eligible patients and their parents about the study and ask them to participate in the study. If informed consent is given, diagnostics will be carried out.

#### Randomization and blinding

Computerized lists for familywise randomization with variable block length stratified by recruitment centers are prepared by the Department of Medical Biometry and Epidemiology of the University Medical Center Hamburg-Eppendorf. According to a 2x2 factorial study design, each family is randomized to one of four combinations of the two interventions (CARE-FAM only, WEP-CARE only, combination, no study intervention). The subsequent central allocation procedure will be managed by the coordinating study center in Hamburg to guarantee allocation concealment. Randomization will take place once the standardized baseline diagnostics are complete. Thus, every randomized family received comprehensive standardized diagnostics of every participating child and parent. This will maintain the families’ interest in the study and enhance retention. Although families will be aware of the group they have been assigned to, the external raters assessing the primary outcome and the health-economics will be blinded regarding the families’ group allocation to avoid detection bias by project members.

